### Randomization and blinding procedure

#### Randomization

The computer-generated randomized allocation sequencer will be imported into the Viedoc eCRF system and made available to testing administrators. Only testing administrators will have access to participant treatment allocation and the allocation will not be available until the participant has signed the informed consent and deemed eligible to participate in the study.

This investigation will use a list randomization recruitment method [50] for CVI where participants will be randomly allocated to receive one of the four treatment groups: tVNS #1 (active); tVNS #2 (sham); MNRB #1 (active); MNRB #2 (sham). The randomization will be stratified by sex (male = 1, female = 2) and cardioactive medications (yes = 1, no = 0) with varying block size within strata. Viedoc will generate the randomization number as well as the allocated treatment group for each participant.

Participants will be considered as taking cardioactive medication if they report that they are currently taking any medication for high BP, cholesterol, heart disease, or prescription pain medication. Participants will also be considered as taking cardioactive medication if they answer that they use tranquilizers, antidepressants, and/or antipsychotics either “less than every week,” “every week, but not daily,” or “daily.” Participants are permitted to continue taking any previously prescribed pain medications/psychopharmacological treatments that are necessary during the trial period.

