#### Blinding

The blinding strategy utilized in this clinical trial follows guidelines previously set forth and designed specifically for non-pharmaceutical intervention trials [51]. As recommended [52], research design elements such as treatment type, active and inactive treatment mechanisms, and research hypotheses are concealed from participants, testing administrators, and data collectors. Active and sham treatment allocation is concealed from the participants and testing administrators. Both testing administrators and study participants will be told that they will provide/receive two different *versions* of nerve stimulation at different locations on the ear (for the tVNS group) or that there are two breathing techniques that are being explored (for the MNRB group) in this investigation [53]. The testing administrators will introduce either “Version 1” (active) or “Version 2” (sham) of the treatment interventions.

The principal investigators ([name] and [name]) are blinded to patient treatment allocation as well as the randomization form in Viedoc. This form will only be visible to the testing administrators performing participant data collection. To protect against export of blinded data during the study, there will be two export roles in this study: (1) blinded export and (2) unblinded export. Blinded data export role will be given to the investigators prior to database lock while the unblinded data export role will be given to the investigators only after database lock.

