#### ViedocMe

Participant-reported outcome measures (PROMs) in the form of questionnaires (see below) will be completed electronically using the ViedocMe functionality available in Viedoc at CVI and CVII. Study staff will create a ViedocMe account for each participant in the participant’s Clinic View in Viedoc and provide a unique log-in profile (username, pin code, and ViedocMe web address) for each participant. Participants are to use this information to log in to their personal ViedocMe account on a tablet (Samsung Galaxy Tab A6 32GB) which is connected to Oslo University Hospital’s secure wireless account. The questionnaires in ViedocMe will only be available for completion the day of each clinic visitation. Participants will complete the questionnaires at the end of each visitation. After the time-window has expired (i.e., at midnight on the day of the clinic visit), questionnaires can no longer be completed electronically. If problems arise using ViedocMe, or if the participant prefers to use paper forms, paper copies of the questionnaires will be handed out to the participant and the data will be entered into Viedoc by testing administrators. Questionnaires are only available to participants in Norwegian. For a list of names with descriptions of each questionnaire utilized in this study, see the Appendix.

List of questionnaires in the order of their completion:

Credibility Expectancy QuestionnaireParticipant Global Impression of ChangeEQ-5D-5LHopkins Symptom ChecklistMultidimensional Assessment of Interoceptive Awareness, version 2Spiritual and Religious Attitudes in Dealing with IllnessPain catastrophizing scaleBrief Pain InventoryInsomnia Sleep InventoryOswestry Low Back Pain Disability QuestionnaireGeneral Health Questionnaires

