**Fig. 6 Fig6:**
[figure not shown]
Clinical visitations. **a** Clinical visitation 1 (CVI). **b** Clinical visitation II (CVII)

The assigned testing administrator will then conduct a clinical interview at CVI in order to confirm a diagnosis of FM, including FM, and in CVII in order to determine how or if the pain has changed. Participants will be guided through an electronic version of the 2016 revision to the 2010/2011 FM diagnostic criteria form [44] digitalized in Viedoc by the lead author ([name]). Prior to the FM diagnostic confirmation interview, participants will be asked to numerically rate their pain in the following manner: “On a scale of 0 to 10, where 0 corresponds to no pain and 10 corresponds to the worst possible pain you can imagine; (1) How strong would you say that the pain usually is?; and (2) How strong is the pain now?” If participants are confirmed to have FM with an average (i.e., usual) pain intensity NRS ≥ 6, they are instructed to remain seated in a semi-Fowler position (no more than 30° from the horizontal), with eyes closed, and breathe normally without speaking or making any movements [47]. For CVII, there are no diagnostic criteria cutoffs for FM and average pain intensity.

The testing administrator will then conduct a visit compliance interview immediately following the FM diagnostic interview for each visitation. Participants are instructed prior to visitation to follow a normal sleep routine [90] and abstain from any type of intense physical training the day before each clinical visitation [91]. Participants are also asked to abstain from drinking coffee, any type of energizing drinks [92], and tea [93] 2 h before each clinical visitation. Furthermore, participants are instructed not to drink alcohol 24 h prior to their visitations [94] or eat within 2 h of their visitation [95] (eating/digestion [96], missing a meal [97], or smoking [34] can significantly influence HRV). If patients do partake in the aforementioned actions, this information will be accounted for at this time. Upon completion of the visit compliance interview, testing administrators will note the sex of each participant and any cardioactive medications that they are taking. The computer-generated randomized allocation sequencer in Viedoc then generate the randomization number as well as the allocated treatment group for each participant (e.g., tVNS #1 (active); tVNS #2 (sham); MNRB™ #1 (active); MNRB™ #2 (sham)).

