In order to acclimatize to the HRV recording environment, each participant is instructed to remain seated for at least 5 min [98] prior to taking the first HRV measurement (Fig. 7a). Acclimatization helps reduce HRV changes due to posture changes [99, 100] and can also reduce confounds subsequent to participant test anxiety [26]. Immediately following the 5 min acclimatization period, three 1-min HRV recordings will be taken on the tip of the right index finger of each participant separated by 1-min intervals. The beginning and end of each of the three HRV recordings will not be announced due to the impact of attentive states and test anxiety on respiratory frequency [101] and HRV recordings [102]. An average of the last two recordings will be used as the baseline measure.

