For clinical visitation I, each participant will be introduced to their assigned treatment (tVNS or MNRB™) and version (version 1 or 2). Testing administrators are to motivate each participant to complete the treatment and provide instructions on how to use the devices throughout the 2-week intervention period. In addition to a verbal introduction of each treatment version, testing administrators will also guide participants in a short 5-min trial period during which the treatment is properly setup and tested. This is helpful in demonstrating to participants the functionality and design of their treatment. Participants are welcome to ask any questions or share any concerns in regard to the procedure and what is demanded of them at this time. When the treatment introduction and trial period is complete for CVI, participants will receive their Daily Treatment Journal (or return it at CVII) and complete questionnaires in their ViedocMe account (For assessments as a function of timepoints according to the 2013 SPIRIT guidelines, see Table 2). Patients who receive one version of the treatment will be voluntarily offered the second version 6 months after the end of the study if they are still in pain and the results of the study justify this.

**Table 2 Tab2:** Assessments as a function of timepoints (according to the 2013 SPIRIT figure guidelines)

Measure	Target	T0	Intervention	T1
		*Baseline*	*Morning and evening treatment (4 recordings/day)*	*Post-intervention (2 weeks)*
NRS	Average pain intensity	X		X
NRS	Current pain intensity	X	X	X
HRV	Hear rate variability	X	X	X
BMI and WHR	Body mass index and waist-to-hip ratio	X		
BP	Blood pressure	X		X
CPA	Experimental pain threshold, tolerance, and limit	X		X
CEQ	Treatment efficacy expectation	X		
PGIC	Treatment efficacy impression			X
EQ-5D-5L	Health-related quality of life	X		X
HSCL-25	Stress and depression	X		X
MAIA-2	Interoceptive awareness	X		X
SpREUK-15	Spirituality	X		X
PCS	Catastrophizing	X		X
BPI	Pain interference	X		X
ISI	Insomnia	X		X
ODI	Functional disability	X		X
General health	Overall health/nutrition and sociodemographic	X		

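### At the first clinic visit, allocation is generated before baseline HRV, blood pressure and cuff algometry, and the baseline questionnaires follow a trial of the assigned treatment

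*Protocol article*

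**What the plan says.** The protocol article describes CVI under Data collection procedure, Clinical visitations I and II. After consent, body measurements, the two NRS pain ratings, the fibromyalgia interview and the compliance interview, the stratification factors are recorded: "Upon completion of the visit compliance interview, testing administrators will note the sex of each participant and any cardioactive medications that they are taking". The next sentence generates the allocation: "The computer-generated randomized allocation sequencer in Viedoc then generate the randomization number as well as the allocated treatment group for each participant". This fits the Randomization section, under which "the allocation will not be available until the participant has signed the informed consent and deemed eligible". Neither place requires completed baseline measurements first.

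The text then turns to acclimatization and the primary outcome: "Immediately following the 5 min acclimatization period, three 1-min HRV recordings will be taken on the tip of the right index finger". Of these recordings, "An average of the last two recordings will be used as the baseline measure". Blood pressure follows HRV, and cuff algometry follows blood pressure. Only then is the treatment introduced, and "testing administrators will also guide participants in a short 5-min trial period during which the treatment is properly setup and tested". Questionnaires come last; the ViedocMe section says "Participants will complete the questionnaires at the end of each visitation". Table 2 places HRV, blood pressure, cuff algometry and most questionnaires in the T0 baseline column.

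Testing administrators collect all data at both visits. The Randomization section gives them, and nobody else, access to the allocation. Of the randomization form, the Blinding section says "This form will only be visible to the testing administrators performing participant data collection".

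**The concern.** A baseline is meant to be a measurement that allocation cannot have influenced. Here two sets of T0 measurements lack that protection, for different reasons.

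For HRV, blood pressure and cuff algometry, the person running the measurement can already know the allocated group. The article itself notes that attentive states and test anxiety affect HRV recordings, and it lets the administrator end a cuff test. The statistical section analyses the CVI-to-CVII change in HRV, so a baseline difference caused by allocation would enter the effect estimate for the primary outcome.

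For the questionnaires the exposure is more direct. Before answering, the participant has been encouraged by staff and has tried the assigned version. The CEQ also comes first in the stated order, so expected improvement has just been rated. This route runs through the participant and does not depend on assessor blinding.

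**Working it through.** No figure in the plan bears on this point. The sample-size figures do not change with visit order. The check is one of sequence and access.

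**Step 1: order at CVI, read from the text**

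1. Consent; height, weight, BMI and waist-to-hip ratio.
2. NRS usual pain and NRS present pain.
3. Fibromyalgia interview, then compliance interview.
4. Sex and cardioactive medication noted; **allocation generated**.
5. Acclimatization (5 min), then three HRV recordings.
6. Blood pressure.
7. Cuff algometry.
8. Introduction to the assigned version and 5-min trial.
9. Questionnaires.

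Steps 1 to 3 are before allocation. Steps 5 to 7 are after allocation but before the participant meets the treatment. Step 9 is after both.

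**Step 2: who knows what**

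| Measure | Allocation generated? | Participant has met the treatment? | Route for bias |
|---|---|---|---|
| Body measures, both NRS ratings | No | No | None |
| HRV, blood pressure, cuff algometry | Yes | No | Assessor only |
| EQ-5D-5L, HSCL-25, MAIA-2, SpREUK-15, PCS, BPI, ISI, ODI | Yes | Yes | Participant, and possibly staff |
| CEQ | Yes | Yes | Intended: it rates the treatment just introduced |

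PGIC is collected only at CVII and does not arise here.

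**Step 3: does the assessor know active from sham?** The statements do not agree:

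- Randomization: administrators have access to the allocation.
- Blinding: the form is visible to them, yet active or sham status is said to be concealed from them, and they introduce Version 1 or Version 2.
- Clinical visitations I and II: the groups generated in Viedoc are printed with the words active and sham.
- Limitations: unblinded experimenters are treated as a limitation.

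On any reading, the administrator can know modality and version number when the baseline is taken. Whether the administrator knows which version is active cannot be settled from the text.

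**Step 4: how a shift would act.** Suppose allocation moves the recorded baseline of one arm by δ relative to its comparator and leaves CVII untouched.

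- Change score (CVII − CVI): the between-group estimate moves by −δ.
- Baseline-adjusted comparison with slope b: it moves by −bδ. With b between 0 and 1 this is smaller than δ, but not zero.
- CVII values alone: it moves by 0.

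The document gives neither δ nor b, so no magnitude follows.

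**Step 5: how far recruitment had gone.** From Trial status: start 6/5/2019, end 8/1/2020, protocol version 3 dated 4/27/2020.

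- Window: 423 days. Elapsed at version 3: 327 days. 327/423 = 77%.
- If accrual was steady (an assumption), those remaining are 112 × 96/423 ≈ 25, or 25/4 ≈ 6 per arm.

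**The case against.** The strongest reply is that the physiological baselines are well protected in practice. The participant is still unaware of the treatment. HRV is computed by an app from three unannounced recordings with a fixed averaging rule, and the participant sits with eyes closed and silent. In cuff algometry the participant holds the rating scale and the stop button. If the concealment statement in the Blinding section holds, the administrator has a version label but no known direction in which to lean. This stands as a reason to think any shift is small. It does not remove the route, and it rests on one side of an unreconciled contradiction.

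For the questionnaires, HSCL-25 asks about 14 days and the ISI usually about a month, so a 5-minute demonstration may move answers little. That is fair, and no shift is shown. The answers are still given after the treatment has been met, which is not what a T0 baseline column implies.

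Figures 6 and 7, which depict the visit order, are not available here, and the text is not strictly chronological throughout. The order of the steps at issue is nevertheless given in words.

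A reader might infer more than the document supports:

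- **That every CVI-to-CVII change is affected.** The statistical section names three such changes: HRV, NRS present pain and NRS average pain. Both NRS baselines precede allocation. The daily home recordings do not use the CVI baseline either.
- **That administrators certainly know active from sham.** The text says both.
- **That the bias can be sized**, for example as a 0.2 SD shift against the 0.9 effect size (0.2/0.9 = 22%). The 0.2 has no source in the document, and 0.9 is the article's threshold for a large effect, not a stated effect in SDs of the CVI-to-CVII change.
- **That participants unable to complete HRV or algometry are lost after randomization.** The order permits this, but the document gives no sign of how often it would occur.

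**Conclusion.** The concern holds in limited form and should be fixed. Baseline HRV, blood pressure and cuff algometry are taken after allocation by staff who can access it. The exposure is through the assessor only, and its strength depends on which statement about assessor blinding is true. The eight baseline questionnaires are completed after the assigned treatment has been introduced and tried, and are not true pre-treatment baselines. This is the clearer part of the finding. Body measures and both NRS ratings are unaffected, and the CEQ is in its proper place.

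The size of any bias cannot be computed. The conclusion assumes that the order in the text is the order followed at the visit. Reordering CVI would not settle the question of assessor blinding at CVII.

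**What to change.** **Remaining participants.** Generate the allocation in Viedoc only after HRV, blood pressure and cuff algometry are recorded. Have all baseline questionnaires except the CEQ completed after those measures, so that resting HRV conditions do not change, and before randomization and treatment introduction. Keep the CEQ after the introduction.

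**Blinding text.** Reconcile the Randomization, Blinding, Clinical visitations and Limitations sections, so that it is clear whether administrators see active and sham labels or version numbers only.

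**Participants already enrolled.** Flag them, disclose the order in the report, and interpret questionnaire changes from CVI with caution. Add, as a sensitivity check, a between-group comparison of CVII values that does not use the CVI baseline. This is better than excluding those measured in the present order, which under steady accrual would leave about 6 per arm. The CVII-only comparison gives up whatever precision the baseline would have added.

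**Cost.** An eCRF order change, a short amendment and two baseline procedures within one trial. No new measurement or visit is needed.

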**Fig. 7 Fig7:**
[figure not shown]
Data collection timeline. **a** Heart rate variability. **b** Blood pressure. **c** Computerized cuff-pressure algometry

At least 2 min following the three HRV recordings, resting systolic, diastolic, and mean blood pressure (BP) will be measured (Fig. 7b). The correct size cuff is chosen after the circumference of the upper arm is determined. Three readings on the upper right arm are taken separated by 1-min intervals. The average of the last two measurements will be used in the analyses [103]. This BP assessment protocol is similar to that used in several population studies [104–106].

Following the BP assessment, CPA will be administered (Fig. 7c). Participants are asked to continuously rate perceived pain if the sensation of pain increases, decreases, or remains the same, by using the electronic VAS module which is placed in their dominant hand. The VAS ranges from 0-cm (no pain) to 10-cm (worst pain imaginable). Furthermore, participants are instructed to press a red stop button located directly below their VAS console if and when the sensation of pain becomes intolerable at any time. The testing administrator conducting the data collection will also have the ability to stop the exercise at any moment if needed via the computer. Three CPA sessions will be recorded on each leg individually: first the left leg, then the right leg, and finally the left leg, each separated by a 30-s interval. The average of all three sessions will be used in the final analyses.

For clinical visitation I, each participant will be introduced to their assigned treatment (tVNS or MNRB™) and version (version 1 or 2). Testing administrators are to motivate each participant to complete the treatment and provide instructions on how to use the devices throughout the 2-week intervention period. In addition to a verbal introduction of each treatment version, testing administrators will also guide participants in a short 5-min trial period during which the treatment is properly setup and tested. This is helpful in demonstrating to participants the functionality and design of their treatment. Participants are welcome to ask any questions or share any concerns in regard to the procedure and what is demanded of them at this time. When the treatment introduction and trial period is complete for CVI, participants will receive their Daily Treatment Journal (or return it at CVII) and complete questionnaires in their ViedocMe account (For assessments as a function of timepoints according to the 2013 SPIRIT guidelines, see Table 2). Patients who receive one version of the treatment will be voluntarily offered the second version 6 months after the end of the study if they are still in pain and the results of the study justify this.

**Table 2 Tab2:** Assessments as a function of timepoints (according to the 2013 SPIRIT figure guidelines)

Measure	Target	T0	Intervention	T1
		*Baseline*	*Morning and evening treatment (4 recordings/day)*	*Post-intervention (2 weeks)*
NRS	Average pain intensity	X		X
NRS	Current pain intensity	X	X	X
HRV	Hear rate variability	X	X	X
BMI and WHR	Body mass index and waist-to-hip ratio	X		
BP	Blood pressure	X		X
CPA	Experimental pain threshold, tolerance, and limit	X		X
CEQ	Treatment efficacy expectation	X		
PGIC	Treatment efficacy impression			X
EQ-5D-5L	Health-related quality of life	X		X
HSCL-25	Stress and depression	X		X
MAIA-2	Interoceptive awareness	X		X
SpREUK-15	Spirituality	X		X
PCS	Catastrophizing	X		X
BPI	Pain interference	X		X
ISI	Insomnia	X		X
ODI	Functional disability	X		X
General health	Overall health/nutrition and sociodemographic	X		

#### Daily intervention procedure (Fig. 8)

Upon waking or going to sleep, participants are to take a 1-min HRV recording with CameraHRV before and after their assigned 15-min treatment intervention. Participants are instructed to use the same HRV recording procedure as in CVI and CVII: sitting in a relaxed semi-Fowler position no more than 30° from the horizontal, knees at a 90° angle, while breathing normally, with both feet flat on the floor without moving or talking. Due to the fact that circadian rhythms and digestion have an impact upon HRV [107, 108], time of day and time since last meal should be standardized when possible in short-term HRV recordings, especially for designs incorporating repeated recordings over time [26]. Therefore, participants are instructed to take their HRV recordings preferably at the same time every day in the morning and at night before and after their assigned intervention. Furthermore, participants are instructed to keep a normal sleep schedule throughout their 2-week intervention while abstaining from consuming any large meals, caffeinated drinks, nicotine, or alcohol immediately prior to their morning HRV recordings and no less than 2 h before their evening HRV recordings. HRV recordings will be saved locally on the assigned Krüger&Matz Flow 5 phone and labeled with the participant’s assigned Viedoc identification number. Participants are to legibly encircle their NRS after each 1-min HRV recording (four times per day) in their Daily Treatment Journal throughout the 2-week intervention period.

